## Abstract

**Background:**

Atopic eczema (AE) is a common skin problem that impairs quality of life and is associated with the development of other atopic diseases including asthma, food allergy and allergic rhinitis. AE treatment is a significant cost burden for health care providers. The purpose of the trial is to investigate whether daily application of emollients for the first year of life can prevent AE developing in high-risk infants (first-degree relative with asthma, AE or allergic rhinitis).

**Methods:**

This is a protocol for a pragmatic, two-arm, randomised controlled, multicentre trial. Up to 1400 term infants at high risk of developing AE will be recruited through the community, primary and secondary care in England. Participating families will be randomised in a 1:1 ratio to receive general infant skin-care advice, or general skin-care advice plus emollients with advice to apply daily to the infant for the first year of life. Families will not be blinded to treatment allocation. The primary outcome will be a blinded assessment of AE at 24 months of age using the UK Working Party Diagnostic Criteria for Atopic Eczema. Secondary outcomes are other definitions of AE, time to AE onset, severity of AE (EASI and POEM), presence of other allergic diseases including food allergy, asthma and hay fever, allergic sensitisation, quality of life, cost-effectiveness and safety of the emollients. Subgroup analyses are planned for the primary outcome according to filaggrin genotype and the number of first-degree relatives with AE and other atopic diseases. Families will be followed up by online and postal questionnaire at 3, 6, 12 and 18 months with a face-to-face visit at 24 months. Long-term follow-up until 60 months will be via annual questionnaires.

**Discussion:**

This trial will demonstrate whether skin-barrier enhancement through daily emollient for the first year of life can prevent AE from developing in high-risk infants. If effective, this simple and cheap intervention has the potential to result in significant cost savings for health care providers throughout the world by preventing AE and possibly other associated allergic diseases.

**Trial registration:**

ISRCTN registry; ID: ISRCTN21528841. Registered on 25 July 2014.

**Electronic supplementary material:**

The online version of this article (doi:10.1186/s13063-017-2031-3) contains supplementary material, which is available to authorized users.

## Background

Atopic eczema (syn. atopic dermatitis or eczema) [1] is a very common chronic skin problem affecting 16 to 30% of UK children and around 20% worldwide [2, 3]. Atopic eczema usually starts in infancy and around 40% of cases persist into adulthood, especially those with early onset and widespread disease [4]. The family impact of caring for a child with moderate or severe atopic eczema is greater than that in caring for children with type 1 diabetes mellitus, mainly due to sleep deprivation, employment loss, time to care for atopic eczema and financial costs [5].

Children with atopic eczema, especially those with severe disease, are at increased risk of also developing other allergic (immunoglobulin E (IgE)-mediated) diseases including food allergy, allergic asthma and allergic rhinitis (hay fever) [6–8]. Eczema is often the first manifestation of the so-called ‘atopic march’, in which a child progresses from atopic eczema to food allergy, asthma and allergic rhinitis later in life [9, 10]. Together, these atopic diseases are the most common chronic diseases of childhood and represent a major financial burden to the UK National Health Service (NHS), with direct costs estimated at over £1 billion per annum in 2004 [11]. There is a strong association between atopic eczema during infancy and the risk of food allergy, with the highest prevalence of food allergy reported in early onset and severe atopic eczema. A causal link has been proposed [12], and this is supported by evidence from mouse and human studies showing that sensitisation to some foods can occur across a defective skin barrier [13, 14].

Atopic eczema is highly heritable and shows strong familial clustering. Prevalent mutations in the gene encoding filaggrin (*FLG*), a key skin-barrier protein, represent the strongest and most consistent known genetic risk factor for atopic eczema [15, 16].

Emollient (moisturiser) therapy is intended to improve the barrier function of the skin. An emollient provides lipids to the stratum corneum, which in turn, improves skin hydration by trapping water. Emollients also help to prevent inflammation caused by external irritants as evidenced by their benefit in preventing irritant occupational hand eczema [17]. In premature babies, emollients have been shown to reduce the incidence of skin inflammation [18], and in people with atopic eczema, to reduce flares of atopic eczema (secondary prevention) [19].

Primary prevention is a highly desirable goal in a complex chronic disease like atopic eczema with no cure. If primary prevention of atopic eczema using a strategy of early skin-barrier enhancement with simple low-cost emollients is effective, it would represent a significant cost saving for health care providers through reduced treatment and appointment costs. Further cost savings would result if early skin-barrier enhancement prevents sensitisation and associated food allergy, asthma or allergic rhinitis [11]. Even if the frequency of atopic eczema cannot be significantly reduced, a shift in the severity distribution of atopic eczema towards milder cases could improve quality of life and reduce carer burden and health care provider costs.

We carried out pilot studies to inform the design of this trial. A functional mechanistic study provided evidence for the choice of emollients for this trial and showed they are not associated with any harm to the skin barrier [20]. A multicentre, randomised controlled pilot trial of 124 families showed that families found the intervention acceptable and thus it would be feasible to conduct a larger trial of emollients for the prevention of atopic eczema [21]. Clinical outcomes showed that infants in the emollient group had a significantly reduced risk of developing atopic eczema by 6 months of age compared to those in the control group (43% versus 22%, respectively, relative risk, 0.50; 95% CI, 0.28–0.90; *P* = .017). A further trial from Japan that included 118 infants showed similar results, with 32% fewer infants in the emollient group developing atopic eczema [22]. This large, pragmatic trial (the Barrier Enhancement for Eczema Prevention (BEEP) trial) described here is now required to confirm the results seen in these small, short-term trials and to establish the long-term effects of emollients for preventing atopic eczema and associated allergic diseases.

This is an abridged protocol based on protocol version 5.0 dated 26 October 2016. The full protocol is available on the trial website [23]. This protocol adheres to the Standard Protocol Items: Recommendations for Interventional Trials (SPIRIT) recommendations for interventional trials and the SPIRIT Checklist is included (see Additional file 1).

### Objectives

The main objective is to determine whether applying emollient daily to the entire body surface area for the first year of life can prevent atopic eczema in high-risk childrenOther objectives are to investigate:
○ Whether emollients can delay the onset and/or reduce the severity in those who develop atopic eczema○ Whether emollients can prevent other allergic diseases developing○ The safety and cost-effectiveness of the prevention strategy○ The role of *FLG* genotyping as possible stratifier of response to emollient intervention

## Methods/design

### Trial design

This is a randomised, controlled, two-arm (skin-care advice plus emollient versus skin-care advice alone), parallel-group, multicentre, assessor-blind trial (Fig. 1). It is a pragmatic design in which investigators have no scheduled contact with the families between randomisation and the 24-month visit in order to limit any influence on adherence, minimise the risk of un-blinding and keep the research nurse resources required to a reasonable level. All other contact is with the trial coordinating centre (Figs. 2 and 3). Screening for eligibility and the consent process is carried out either antenatally or shortly after delivery. Further eligibility checks are carried out post delivery prior to randomisation which takes place within 3 weeks of delivery.

**Fig. 1 Fig1:**
[figure not shown]
Schematic diagram showing the trial design and duration for participating families

**Fig. 2 Fig2:**
[figure not shown]
Flowchart indicating participant flow through the trial

**Fig. 3 Fig3:**
[figure not shown]
Standard Protocol Items: Recommendations for Interventional Trials (SPIRIT) figure showing important events in the trial and their respective time points. EASI - Eczema Area and Severity Index, POEM Patient Oriented Eczema Measure, EQ-5D-5 L – EuroQol Five Dimension, CHU-9D – The Child Health Utility. ^1^The 24 month is a face-to-face visit from the research nurses blinded to treatment allocation. ^2^Hayfever status assessed at 60 month only. ^3^Washing practices only

### Setting

The trial is recruiting families across England. Identification is via primary care (mailshot invitations to participate), secondary care (through antenatal care, dermatology clinics and posters), and in the community via direct advertising. Recruiting sites are mainly secondary care centres, with a smaller number of primary care centres involved. A list of recruiting centres can be found in the acknowledgements.

### Participants

Infants at high-risk of developing atopic eczema, defined as having a first-degree relative with parent-reported physician-diagnosed atopic eczema, asthma or allergic rhinitis, are eligible for the trial. The infant must be no more than 21 days old at the point of randomisation, the mother must be aged at least 16 years and the consenting adult must be able to understand English. Infants are not eligible if they are born prior to 37 weeks’ gestation, have a severe skin condition at time of randomisation that would make it difficult to assess the skin for signs of atopic eczema or that would preclude the use of emollients (such as dystrophic epidermolysis bullosa, ichthyosiform erythroderma or lamellar ichthyosis), or if they have a serious health issue that would make participation difficult for the family (e.g. neonatal sepsis or major congenital abnormalities). Only the first born of any multiple births will be randomised.

### Intervention

Both groups receive general skin-care advice to avoid soap and bubble bath, use mild cleansers and shampoos that have been specifically designed for babies, and avoid using baby wipes based on NICE guidance on infant skin care, July 2006 [24]. The use of bath oils is also discouraged unless directed to do so by a health care professional. Furthermore, the intervention group receives additional advice to apply emollient daily for the first year of life and are supplied with emollient free of charge. Parents are able to choose between Doublebase Gel® (Dermal Laboratories Ltd.) and Diprobase Cream® (Merck Sharp & Dohme Ltd.) and can switch emollient during the trial should they wish to. These emollients were chosen because they have a similar formulation to many emollient creams used in the UK, which would mean that the results of this trial would be applicable to a range of emollients with similar formulation and not restricted to the two emollients used in this trial. Emollients containing sodium lauryl sulphate (SLS) as an emulsifier were specifically excluded because they have been shown to have negative effects on the skin barrier [25]. The skin-care advice for both groups is sent to families within 2 days of randomisation in the form of a booklet and a short online video. These materials will be available as part of the final trial report.

The intervention group advice includes how to apply the emollient; at least once daily all over the infant (the scalp can be avoided) and the emollient should always be applied bathing, even if it has previously been applied that day. Parents are advised to start the emollient as soon as possible after birth and definitely within 3 weeks and the start date of emollient usage is recorded by the trial coordinating centre during a routine 2-week post-randomisation phone call. Emollient is continued until the child is 1 year old and with parental reported usage collected at 3, 6 and 12 months. The trial coordinating centre keeps a record of the quantity of emollient provided to each participating family.

If the infant develops skin problems during the trial, parents are advised to seek medical help in the usual way. Any eczema that develops will be treated as per normal practice regardless of treatment group allocation.

### Primary outcome

The primary outcome is a diagnosis of atopic eczema at 24 months, defined as meeting the UK Working Party Diagnostic Criteria for Atopic Eczema [26] which assesses signs and symptoms present over the past year. The criteria will be applied by a trained research nurse blinded to treatment allocation. Applying these criteria when the infants are 24 months old will detect atopic eczema that has developed between the ages of 12 and 24 months and will, therefore, exclude transient eczematous rashes common in the first year of life that are often not true atopic eczema. Measuring the outcome at 24 months also ensures that any observed effect on reducing atopic eczema prevalence is a true preventative effect rather than a treatment effect of the emollient caused by shifting those with mild atopic eczema into the subclinical range.

### Secondary outcomes

The secondary outcomes relate to outcomes up to and including the 24-month time point:Presence of atopic eczema between birth and 24 months defined as:
 Parental report of a clinical diagnosis of atopic eczema Parental completion of UK Working Party Diagnostic Criteria for Atopic Eczema at 12 and 24 months (Additiona﻿l file 2)
Presence of visible atopic eczema at 24 months (assessed by a trained research nurse blinded to treatment allocation)Time to onset of atopic eczema:
 First parental report of a clinical diagnosis of atopic eczema First topical corticosteroid and/or immunosuppressant prescription for atopic eczema
Severity of atopic eczema:
 Eczema Area and Severity Index (EASI) (Additional f﻿ile 3) at 24 months and Patient-oriented eczema measure (POEM) (Additional file 4) at 12 and 24 months. EASI and POEM are the core outcome instruments recommended by the Harmonising Outcome Measures for Eczema (HOME) for measuring clinician-reported signs and patient-reported symptoms respectively [27, 28] and are both well validated [29, 30]. The EASI will be completed by a trained research nurse who is blinded to treatment allocation
Presence of other allergic diseases:
 Parental-reported wheezing, allergic rhinitis and food allergy symptoms, and parental report of a clinical diagnosis of food allergy between 12 and 24 months Allergic sensitisation at 24 months to any of the following common allergens: milk, egg, peanut, cat, grass pollen, house dust mite Confirmed diagnosis of food allergy at 24 months to milk, egg, and/or peanut derived from a combination of parental report, allergic sensitisation and (if required) food challenge
Health-related quality of life:
 Child quality of life using the Child Health Utility 9D (CHU-9D) at 24 months Parental quality of life measured using the EuroQol-5D-5 L (EQ-5D-5 L) at baseline and 24 months
Health economic outcomes:
 Disease-related health care resource use Cost-effectiveness and cost-utility at 24 months (combining health resource use and health-related quality of life outcomes). If significantly more effective than usual care at 24 months, a longer-term economic model from birth to 16 years we be developed

### Safety outcomes

Safety of the emollient determined from the number of skin infections and infant slippage incidents related to emollient use during the intervention period.

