### Randomisation, allocation concealment and blinding

The randomisation schedule (1:1 ratio) is based on a computer-generated pseudo-random code using random permuted blocks of randomly varying size. It was created by the Nottingham Clinical Trials Unit (NCTU) and is held on a secure University of Nottingham server. During the trial, access to the sequence is confined to the IT programmer at NCTU. Randomisation is stratified by recruiting centre and number of immediate family members (parents or siblings) with atopic disease (1, 2, or more than 2). Recruiting centre staff randomise participants via a web-based randomisation system developed and maintained by NCTU. Recruiting centre staff are not sent the results of the randomisation. It is not possible to blind parents as to which group they are in, but the trial nurses conducting the skin examination at the 2-year visit are blinded to treatment allocation.

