### Planned analysis

Analysis of the primary, secondary and safety outcomes will be performed when all the 24-month data have been collected. The longer-term tertiary outcomes will be analysed once data collection is complete for the 60-month follow-up.

The main approach to all analyses will be to analyse participants as randomised (intention-to-treat), regardless of adherence with allocation and without imputation for missing data. All analyses will be carried out using Stata/SE 13 or above [36].

The primary outcome will be analysed using a generalised linear model adjusting for stratification variables. The difference between the two groups will be summarised using a relative risk with 95% confidence intervals. Sensitivity analyses will be performed using multiple imputation for missing outcomes by including any prognostic variables showing a baseline imbalance in the model and accounting for actual emollient use. Analyses of secondary and long-term outcomes will use appropriate regression models depending on the type of outcome and differences between the two groups summarised with 95% confidence intervals. Descriptive analysis of safety endpoints will be presented both according to randomised group and according to actual emollient use in the two groups. Planned subgroup analyses will be conducted by including an interaction term in the regression analysis for the primary outcome according to: (1) whether an individual is *FLG-*wild-type genotype or whether they have one or two of the screened *FLG* null mutations, (2).the number of immediate family members with atopic disease and (3) the number of immediate family members with atopic eczema.

Full details of the analyses and potential sensitivity analyses for the food allergy/sensitisation outcomes will be documented in the Statistical Analysis Plan prior to any analysis and made publicly available on the trial website [23].

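### The safety endpoint can be read as counting only infections attributed to emollient, and no randomised effect estimate with a confidence interval is stated for harm

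*Protocol article*

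**What the plan says.** Under Objectives, the protocol article lists "The safety and cost-effectiveness of the prevention strategy" among the questions to be investigated. The Safety outcomes section is a single sentence, which judges the emollient's safety by the "number of skin infections and infant slippage incidents related to emollient use during the intervention period".

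Under Planned analysis, the general rule is: "The main approach to all analyses will be to analyse participants as randomised (intention-to-treat), regardless of adherence with allocation". The primary outcome gets a relative risk with a 95% CI. For the next tier, "Analyses of secondary and long-term outcomes will use appropriate regression models depending on the type of outcome", again with 95% CIs. For safety the text is: "Descriptive analysis of safety endpoints will be presented both according to randomised group and according to actual emollient use in the two groups". No effect measure or interval is stated for it.

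Two other statements bear on the point. In the section on randomisation and blinding: "It is not possible to blind parents as to which group they are in". In the Intervention section: "Any eczema that develops will be treated as per normal practice regardless of treatment group allocation".

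**The concern.** There are three linked problems.

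1. **What is counted.** If infections count only when linked to emollient, the arms are counted on different bases. An infant with no emollient exposure has no route to an event. Analysing as randomised does not repair an endpoint that only exposed infants can meet.
2. **How harm is estimated.** Every other tier of outcome is given an interval, whereas safety is given description. The intervention is preventive and is given to newborns. The Trial oversight section dispenses with a separate data monitoring committee because risk is presumed very low, so an interval that tests this presumption would be useful.
3. **The second table.** Emollient use can follow skin disease in either arm, and infection plausibly follows skin disease too. A user versus non-user table can then show excess infection even if emollient is harmless. Stopping emollient after a skin problem would push the other way, so the net direction is uncertain.

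At stake is either a false alarm or false reassurance about the main safety endpoint.

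**Working it through.** **The plan's own figure.** No figure is stated for safety; the only one is the total of 1282 for the primary outcome. With 30% v 21%, two-sided 5% and 90% power, the continuity-corrected formula gives 513 per arm, and 2 × 513 / 0.8 = 1282.5. This matches 1282 within rounding. Without the correction it is 491 per arm and a total of 1228.

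**Inputs.** About 1400 randomised 1:1 gives 700 per arm. Applying the plan's 20% attrition gives 700 × 0.8 = 560. That allowance is for 24 months, so it is probably cautious for first-year events. The article gives no skin-infection risk, no rate of emollient use in controls and no attribution rate. All such values below are assumptions.

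**(a) Attribution, if the clause covers infections.** Assume a true infection risk of 10% in both arms, universal use in the emollient arm, and 25% of users' infections attributed to emollient.
- Emollient arm: 560 × 0.10 × 0.25 = 14 events.
- Control arm, with a proportion u using emollient: 14 × u, which is 0, 2.1 or 4.2 events for u = 0%, 15% or 30%.
- The apparent ratio is 1/u: 3.3 at u = 30%, 6.7 at 15%, and undefined at 0%. It does not depend on the share attributed, and there is no true effect.

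**(b) Actual-use table, counting all infections, no true effect.** Assume eczema in 30%, and infection risk 15% with eczema and 5% without. Assume control infants use emollient in 80% of those with eczema and 20% of those without.
- Overall risk in either arm: 0.3 × 0.15 + 0.7 × 0.05 = 0.080.
- Control users: share 0.3 × 0.8 + 0.7 × 0.2 = 0.38; infected 0.3 × 0.8 × 0.15 + 0.7 × 0.2 × 0.05 = 0.043; risk 11.3%.
- Control non-users: share 0.62; infected 0.080 − 0.043 = 0.037; risk 6.0%.
- Control arm alone: ratio 1.9.
- Both arms pooled, everyone in the emollient arm using: users (0.080 + 0.043) / 1.38 = 8.9%, non-users 6.0%, ratio 1.5.
- Both arms pooled, 90% of the emollient arm using whatever the eczema status: users (0.072 + 0.043) / 1.28 = 9.0%, non-users (0.008 + 0.037) / 0.72 = 6.3%, ratio 1.4.
- Sensitivity: with control use of 40% and 10% and everyone in the emollient arm using, users (0.080 + 0.0215) / 1.19 = 8.5%, non-users 0.0585 / 0.81 = 7.2%, ratio 1.2.

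**(c) Is a randomised estimate worth having?** At 560 per arm and 10% risk in both arms:
- Risk ratio: the 95% CI is the estimate multiplied or divided by exp(1.96 × √(2 × 0.9 / (0.1 × 560))) = 1.42.
- Risk difference: half-width 1.96 × √(2 × 0.1 × 0.9 / 560) = 3.5 percentage points. It is 1.6, 2.6 and 4.2 points at risks of 2%, 5% and 15%.
- Power for a risk ratio of 1.5: 72% at a control risk of 10%, 90% at 15%, but only 41% at 5% and 19% at 2%.

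The interval is informative if infections are reasonably common and wide if they are rare. It is worth reporting in either case.

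**The case against.** The strongest reply is that the planned presentation already includes the randomised groups, in the same sentence as the actual-use table and under a general as-randomised rule. A reader might infer that safety will rest only on an attributed count and a confounded comparison. The article does not support that: the actual-use table is additional, and showing harms by exposure is a common companion when adherence is uncertain. This objection stands. What remains is that neither presentation is marked as primary.

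Second, the attribution clause may qualify slippage alone, where it fits naturally. A table by actual use would also make little sense if non-users could have no events. This partly stands: infections as an attributed count is one reading, not a settled fact. But slippage carries the clause on either reading and would go into the same table, so the table does not decide the matter. Nor does the article say who would attribute events; that this would happen without blinding is inferred from the parents' awareness of allocation.

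Third, this is an abridged article that defers detail to an analysis plan, and descriptive safety reporting is common. A reader might infer that no interval for harm will ever be produced. The text states none but does not exclude one.

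Fourth, the ratio of 1.9 in (b) might be taken as the size of the bias in this trial. It describes a control arm alone. Half of this trial is supplied with emollient, and pooling dilutes the figure.

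**Conclusion.** The point holds as a should-fix improvement. The endpoint sentence has two readings that give different safety results. On one of them, control infants not using emollient cannot contribute infections, and an apparent ratio of 3.3 or more could arise with no true effect if at most 30% of controls use emollient. The stated analysis names no primary safety comparison and no effect estimate or interval, although safety is an objective.

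The actual-use table could show a pooled ratio of about 1.4 to 1.5 with no true effect, and about 1.2 if fewer controls use emollient. These sizes rest on assumed eczema, use, infection and attribution rates, none of which the article gives. They show that the problem can be material, not how large it will be. The unquantified effect of stopping emollient after a skin problem could offset part of the actual-use distortion. None of this bears on the primary outcome.

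**What to change.** **Safety outcomes.** State that all skin infections and all slippage incidents are counted in both arms over the first year, regardless of attributed cause. Report those judged related to emollient as a descriptive sub-line.

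**Planned analysis.** Name the as-randomised comparison as primary for safety, with a risk ratio or rate ratio and 95% CI. Keep the actual-use table, labelled exploratory and non-causal.

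**Cost.** Only wording changes if the questionnaires already ask both arms about skin infections and slippages, which the article does not show; otherwise the questions must be added. Background infections will add noise to the count. Parents remain unblinded, so differential reporting is reduced but not removed.
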